### Primary study parameter(s)

The primary outcome is acceptability of the interventions, assessed during the interview. The two primary acceptability measures are: [1] whether the participant finds the intervention acceptable for dementia care, and [2] whether they want the intervention for themselves. This means, whether persons with dementia want it for themselves, family caregivers for their relative and whether physicians would use it at request. The primary outcome is a categorical variable with three categories (‘yes’, ‘no’ and ‘don’t know’ as a valid answering option).

### Secondary study parameters

The secondary outcomes will be assessed using the survey. Table 1 provides an overview of the instruments per group. When not available, the forward-backward translation technique was used to translate the instruments in all languages necessary for the current study (i.e. Dutch, English, German, Japanese and Hebrew). The instruments were translated to each new language by two native speaking researchers independently. They compared their translations and came to a consensus, followed by back-translation by a professional, independent translator. The translation was reviewed by the two researchers and discussed with a third person, the principal investigator or coordinating local partner. The professional translator and original authors were consulted for any remaining specific questions.

To assess attitudes towards the end of life, we use the death anxiety questionnaire [58] as an indicator of a general or global fear of death as a whole. The response options are *strongly disagree* [1], *disagree* [2], *agree* [3] and *strongly agree* [4], and we added *I don’t know* as an additional option. A sum-score can be calculated by summing the scores of the items with a high score reflecting more anxiety about dying. Also, we selected one item of each of the five subscales of the Death Attitude Profile-Revised (DAP-R) [59, 60] to assess attitudes towards death. including: ‘*The prospect of my own death arouses anxiety in me*’ (Fear of death), ‘*I avoid thinking about death altogether*’ (Death Avoidance), ‘*Death is neither good nor bad*’ (Neutral Acceptance), ‘*I look forward to a life after death*’ (Approach Acceptance), and ‘*I see death as a relief from the burden of this life*’ (Escape Acceptance). We will look at the individual items. The seven response categories were reduced to five to match those of the death anxiety questionnaire. Additionally, we use a single item asking the participants about their general level of comfort with talking about the end of life with the response options *very comfortable*, *somewhat comfortable*, *somewhat uncomfortable*, *very uncomfortable*, *don’t know* [11].

To assess caregiver burden, we use the shortened 6-item version of Zarit’s well-tested caregiver burden interview (ZBI-6) [61–65]. Items are scored on a five-point scale, with a cut-off score of ≥ 13 considered as a clinically significant burden [66]. The items are added up to create a sum-score.

The three items from the subscale ‘Preparation for end of life’ from the Quality at the end of life in terminal patients (QUAL-E) [67, 68] are used to indicate concerns of the person with dementia about the future after they have died. The items are scored on a 5-point Likert scale ranging from *not at all* to *completely*. The items are added up to create a subscale score.

To assess coping strategies in all three groups, we use the Brief COPE subscales Active coping, Planning, Using instrumental support, Using emotional support, Denial, Acceptance, and Religion [69, 70]. Each subscale contains two items that are scored from 1 (*not doing it at all*) to 4 (*doing it a lot*). The items are added up to create the subscale score.

We will use two items about medical decision making. The family caregiver is asked whether their relative is capable of taking decisions on medical treatments by themselves using the response option *yes*, *sometimes or in part*, *no* and *I don’t know* [11]. Next, they are asked to indicate whether their relative’s faith or spiritual background influences decisions about care and treatment using the categories *yes strongly*, *yes somewhat*, *no*, *I don’t know* [11, 71]. The physicians are asked to rate the item *When you think about the goals of future care for your patients with dementia, which of the following do you most strongly consider*? Using the response options *what you think your patient would probably want for themselves*, *what the family/loved one of the patient wants*, *what you as the physician of your patient wants for them* and *don’t know* [11]. We will look at the individual items.

The family caregiver is asked about the type of dementia and the month and year of the diagnosis. As an indicator of the stage of dementia, we will ask the family caregiver to complete the cognitive subscale of the Quick Dementia Rating System (QDRS) [72]. This subscale corresponds to the Mini Mental State Examination classifications (28–30, 24–27, 18–23, 10–17 and 0–9)). The cognitive subscale consist of 4 domains: memory and recall, orientation, decision making & problem solving, and language & communication abilities. Each domain has five possible answers, with higher numbers reflecting more severe cognitive symptoms. The items of QDRS are added up to create a sum-score.

The family caregiver and person with dementia are asked to indicate the extent to which they (dis)agree with the following statement: *The most important goal of [your relative’s] health care is to preserve my [his/her] life as long as possible, even if that requires treatments that may cause pain or discomfort* using a scale ranging from *strongly agree* [1] to *strongly disagree* [5]. *Don’t know* [9] is also a valid option [11]. The family caregiver is also asked to indicate which they most strongly consider when thinking about the goals of care for their relative using the categories *what you think your relative would probably want for themselves*, *what you want for your relative*, *what you think the physician of your relative wants for themselves*, and *don’t know*.

Illness cognition refers to the dementia. All three groups are asked to rate the extent they agree with two statements: *Dementia is a disease you can die from* [11, 37] and *Dementia is a normal part of the ageing process* [73, 74] using the response options *strongly agree* [1] to *strongly disagree* [5] and *Don’t know* [9]. Physicians will also be asked to rate the statement *Palliative care applies from the time of diagnosis to the stage of severe dementia* using similar response categories [75].

Illness perception also refers to the dementia. The person with dementia is asked to rate four selected items of Brief Illness Perception Questionnaire (IPQ-B) [76–78] that are relevant to our research questions. The four items consist of one item from the Consequence, Personal Control, Illness concern and Emotional representation dimensions. The items are scored using a 11-point (0–10) Likert-type scale with higher scores reflecting more negative perceptions. The items are added up to create a sum-score.

Inclusion of other in the self (IOS) was assessed using the IOS Scale [79]. This is a single-item, pictorial measure of relationship closeness. It consists of seven pairs of circles, one that includes the word *self* and one that includes the word *other*, that overlap to different degrees. Family caregivers are invited to select the pair that best describes their relationship with the person with dementia.

Locus of control (i.e., personal belief about whether outcomes of behaviour are determined by one’s actions or by forces outside one’s control) is measured using the 4-item locus of control scale (IE-4) [80]. The items are scored on a scale ranging from *doesn’t apply at all* [1] to *completely applies* [5]. Higher scores on Internal Locus of Control of Reinforcement (Item 1 and 2) relate to higher levels of internality (internal control), while higher scores on External Locus of Control of Reinforcement (Item 3 and 4) relate to higher externality (external control). Internal and External Locus of Control are calculated separately.

To assess possible depression in the person with dementia and their family caregiver, the 2-item Patient Health Questionnaire depression module (PHQ-2) [81] is used. The PHQ-2 asks about the frequency of depressed mood and anhedonia over the past 2 weeks, scoring each as *not at all* (0) to *nearly every day* [3]. The time frame was adjusted to one month, as we were interested in mood over a longer period of time. Additional to rating their own mood, the family caregiver is asked to rate the mood of their relative using these two items.

The item *Have you ever accompanied a member of your family or friend suffering from advanced dementia at the end of their life* is used to measure personal experience with dementia [82]. The item is scored using *yes* [1] or *no* (0).

The family caregiver is asked about their preparedness for the end of life of their relative using the item *If your relative were to die soon, how prepared would you be for their death* [83]. We adjusted the 3 response options to a 7-point scale ranging from 1 (*not prepared at all*) to 7 (*prepared as much as possible*) to allow for greater precision [84].

Demographic information includes age, gender, educational level, country of birth, religious background, worked in healthcare, relation to the person with dementia, living situation of the person with dementia, and work status of the family caregiver. The family caregiver provides the demographic information about the person with dementia. For physicians, we also ask details about their work experience; specialty, additional palliative training, work setting, years of experience with dementia care [82].

Finally, the members of the CONT-END acceptability study research team are asked to fill in a questionnaire about their own attitudes and views regarding the study and acceptability of the four interventions to increase transparency and their reflective awareness. This will be done at the beginning and after the data collection.

### Pilot testing of the instruments

The pilot testing of the items for the survey was conducted in the Netherlands. During a face-to-face visit, the survey for people with dementia was read out loud to one person with dementia (female). Her family caregiver (female) examined the survey for family caregivers. Six people aged over 65 years (five females, one male) received the digital version of the survey for family caregivers. One of them (female) also evaluated the survey for people with dementia digitally. The participants were asked to indicate whether the items were easy to understand and whether they were confronting. Most items were considered clear and not confronting. Items from validated questionnaires were not adjusted despite occasional comments from the participants. The time and effort needed to fill in the survey was also acceptable. Some participants commented that it was difficult to choose one option when they had a nuanced view. Minor adjustments were made in the instructions and response options (for example, changing “agree” and “disagree” if not the endpoint of the scale into “somewhat agree” and “somewhat disagree” for the questions on attitudes about the end of life).

### Development of the animation videos

With a professional media production group, Knowledge Media Research Centre, we developed video vignettes to explain each intervention in a standardized manner, aiming at a neutral stance, not slanted to either acceptance or non-acceptance. We choose animation videos to support understanding with visual and audio cues. Each video includes a brief introduction, an example and a summary of the main aspects of the intervention. To facilitate orientation, each video has its own colour. Further, a mnemonic for each video in the form of a hand-out with screenshots summarizes the content of the animation video for the persons with dementia and their family caregivers. The handout about euthanasia is supplemented with a sheet explaining local rules and explanation of differences with locally better-known PAS or palliative sedation.

The animation videos were developed iteratively navigating the following steps: step 1, developing the scripts; step 2, reviewing, pilot-testing and refining the scripts; step 3, reviewing, pilot-testing and refining the animation videos; step 4, translating and adapting the animation videos into other languages.

Step 1: Developing the scripts. The initial scripts of the animation videos were developed in English. The scripts were written with the goals in mind that they should be applicable in all six countries and understandable for all three groups of participants in this study.

Step 2: Reviewing, pilot-testing and refining the scripts. The initial scripts were reviewed by the CONT-END research team, consisting of an elderly care physician, GP, epidemiologist, communication expert, psychologists, and anthropologist. Next, the partners from the other countries were consulted on whether cultural adjustments were needed. This resulted in minor changes, for example, to replace “euthanasia” in the American and German context with “termination of life on demand” and “Aktive Sterbehilfe”. The independent international Ethics Advisory Committee reviewed the scripts as well. For the euthanasia video, they suggested emphasizing the hypothetical nature of the video to avoid misunderstanding in countries where active euthanasia is illegal. All feedback was discussed within the research team and adjustments were made to the scripts.

The scripts were then translated into Dutch following the forward-backward technique and read out loud during home visits to four pairs of persons with early dementia (three female, one male) and their family caregivers (three female, one male). The family caregivers were the partner or adult children of the persons with dementia. The participants were recruited through GPs. Participants were asked to comment on whether the scripts were easy to understand, neutral, and whether they were confronting. Based on the feedback from the participants, the scripts were thoroughly revised; the language and plot of the videos were simplified, overly positive words, such as “valuable”, were changed into neutral words and the difference between the two ACP interventions was clarified. The English scripts were adjusted accordingly.

Step 3: Reviewing, pilot-testing and refining the animation videos. Based on the updated scripts, Dutch and English animation videos were developed and produced by a team of experts from Knowledge Media Research Centre and a freelance animation artist. The Dutch animation videos were pilot-tested digitally due to COVID-19 related restrictive measures. Eight Dutch participants (five female, three male) with experience with dementia or an age above 65 viewed the animation videos. They were recruited through the Regional Older people Advisory Board connected to the Leiden University Medical Center (LUMC) and via the researchers’ network. In general, the participants found the videos clear and easy to follow. Some participants pointed out that the videos gave the impression that all discomfort could be detected by the technology, and that there were no obstacles for euthanasia once all criteria are met. Potentially confronting elements in the videos were also discussed, for example, the animation of an inflamed lung reminded some people of a COVID19-infection.

The English version of the euthanasia animation video was reviewed by the Ethics Advisory Committee. They suggested adding hand-outs and making the euthanasia procedure more clear for non-Dutch viewers. The English technology video was presented at the Alzheimer’s Association International Conference 2020 [85] to collect feedback from a professional audience. They deemed the animation video suitable. All feedback gathered from this step was discussed within the research team and yet more minor adjustments in scripts and animation videos were made.

Before and after the pilot-testing, readability tests were performed for the scripts with an online tool (available at: https://www.webfx.com/tools/read-able/check.php). The results suggested that almost all of the updated scripts (rated as grade 9 to 10) were more easily readable than the initial versions (grade 10 to 13). The updated script about technology had an average level of grade 9 and should be easily understood by 14 to 15 year-olds. The other three updated video scripts were rated as grade 10, which should be easily understood by 15 to 16 year-olds.

Step 4: Translating and adapting the animation videos into other languages. The English scripts were translated into Hebrew, German, and Japanese using the same forward-backward translation process as for the Dutch scripts. The translated scripts were reviewed by the local partners and at least two older adults (> 65 years) from each country to check whether anything in the scripts was too confrontational or difficult. (Cultural) adjustments in wordings were made when necessary. The Dutch research team and the local partners provided feedback on the timing of the animation videos and approved of the final versions.

### Data analyses

Descriptive statistics will be used to present the acceptability of the four interventions. The internal consistency of the scales will be calculated using Cronbach’s alpha. Descriptive statistics will be calculated to describe the demographics of the respondent groups per country.

We will use logistic regression analyses with acceptability of the intervention as the dependent variable to examine differences in acceptability between group and countries. ‘*Do not know*’ as a response option is often ignored and excluded from the denominator. A dichotomous variable will be create with a denominator of ‘acceptable versus not acceptable plus do not know’. The analyses will be unadjusted and adjusted for the most important life view or personality parameter (religion for euthanasia, planning for the other interventions). We will explore associations between acceptability and participant characteristics (gender, educational level, age, severity of cognitive impairment for persons with dementia, and palliative care training for physicians) and personality (locus of control, coping), depression, medical decision making, professional or personal experience with dementia, physician’s comfort with end-of-life conversations, and caregiver burden, and life view (religion, death anxiety/attitude, preparedness for end of life, priority quality vs. quantity of life, illness cognition). For this, we will use stepwise backward regression analyses. The analyses will be done with and without adjustment for country and group (forced in the stepwise regression analyses).

Qualitative data from the interviews will be used to map possible ambiguity regarding being in control through the interventions, and as to why and in what situation the participant feels the interventions are acceptable. A content analysis regarding acceptability of the interventions will be conducted. Additionally, across all interviews, we will conduct a thematic analysis on perceptions of control. Data collection and data analysis will be executed iteratively. Coding is supported by the software program ATLAS.ti.

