**Methods:**

Cross-sectional mixed-methods vignette study. We assess acceptability of two ACP approaches, technology use at the end of life and euthanasia in persons with dementia, their family caregivers and physicians in six countries (Netherlands, Japan, Israel, USA, Germany, Switzerland). We aim to include 80 participants per country, 50 physicians, 15 persons with dementia, and 15 family caregivers. After viewing each animation video, participants are interviewed about acceptability of the intervention. We will examine differences in acceptability between group and country and explore other potentially associated factors including variables indicating life view, personality, view on dementia and demographics. In the pilot study, participants commented on the understandability and clarity of the vignettes and instruments. Based on their feedback, the scripts of the animation videos were clarified, simplified and adapted to being less slanted in a specific direction.

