### Participants

We initially aimed to include a total of 900 participants from six countries (Netherlands, US, Japan, Israel, Germany, Switzerland), comprising 300 persons with (early) dementia, 300 family caregivers and 300 physicians. From each country, we planned to recruit 50 dyads of persons with dementia and their family caregivers, and 50 physicians. Recruitment procedures for persons with dementia, their family caregivers and physicians are adapted for each participating country in close collaboration with our local partners. We amended the participant target due to difficulty recruiting persons with dementia and family caregivers (see paragraph ‘Adjustments to protocol’).

We work with healthcare professionals, primarily physicians working in memory clinics and hospitals, to recruit dyads of a person with dementia and their family caregiver. We also recruit via general practitioners (GPs) and dementia case managers. When persons with dementia visit their physician, the physician will offer an information package to eligible participants. Participants can then: (a) directly contact the research team, or (b) inform their physician about their decision. The physician will then ask for permission to forward the contact information of the pair to the research team.

For the recruitment of the physicians, the study is announced via relevant webpages and newsletters of local professional networks and educational institutions. The researchers also directly contact physicians who are already in their professional network by email to inform them about the study. The researchers send physicians who are interested an information package about the study and call them to explain the study in more depth and to schedule an appointment for the assessment.

The inclusion criteria for the person with dementia are: (1) has a diagnosis of irreversible dementia established by a physician; (2) has been informed about and is aware of their diagnosis; (3) has a family caregiver who is willing to participate in the study; (4) has decision-making capacity and is able to communicate through sufficient memory and language; (5) is able to understand and sign the consent form; (6) has adequate vision and hearing (can be achieved by using corrective lenses and hearing aid if required); and (7) consents to participate.

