There is no formal capacity test to avoid feelings of failure if that would result in denying participation. We rely on the clinician’s estimation of whether people have capacity to decide to participate in the study and are able to do so. If needed, we provide the referring clinicians with three relevant items of the Dementia Severity Rating Scale to aid clinical judgement of the capacity to give meaningful responses in the interview [56]. For the ‘Memory’ item a score of ≤ 2, ‘Speech and Language’ item a score of ≤ 3, and ‘Ability to make decisions’ item a score of ≤ 2 indicate sufficient ability for the purpose of this study. If the person with dementia is currently affected by a severe psychiatric disorder (e.g., major depression, schizophrenia, substance abuse, post-traumatic stress disorder) as diagnosed by a psychiatrist, psychologist, or physician, or if the participant is expected to die in a few weeks, they are excluded.

Family caregivers can participate if (1) they are willing and able to participate in the study; (2) the person with dementia they care for is willing and able to participate; (3) are ≥ 18 years old. Physicians can participate if they practice a specialty that includes provision of end-of-life care for persons with dementia. Depending on the country, the specialty could be primary care physicians such as GPs, elderly care physicians, geriatricians, geriatric psychiatrists, neurologists, and palliative care physicians.

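### Persons with dementia and caregivers enrol only as pairs, but the pooled logistic regression makes no provision for pairing: the patient–caregiver standard error comes out too large and country standard errors modestly too small

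*Protocol article*

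**What the plan says.** **Enrolment is paired from both sides.** Under Participants, a person with dementia qualifies only if he or she "has a family caregiver who is willing to participate in the study", and a caregiver only if "the person with dementia they care for is willing and able to participate". The Abstract gives the amended target: "We aim to include 80 participants per country, 50 physicians, 15 persons with dementia, and 15 family caregivers". With a one-to-one link, that is 15 pairs in each country.

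**The second primary measure has a shared referent.** Primary study parameter(s) defines it as "whether persons with dementia want it for themselves, family caregivers for their relative and whether physicians would use it at request". The patient and the caregiver are therefore asked about the same individual.

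**The model.** Data analyses says: "We will use logistic regression analyses with acceptability of the intervention as the dependent variable to examine differences in acceptability between group and countries". The models are run unadjusted and adjusted for religion (euthanasia) or planning (the other interventions). For the exploratory stepwise models it adds: "The analyses will be done with and without adjustment for country and group (forced in the stepwise regression analyses". No dyad effect, clustered variance or matched analysis is named.

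**The amendment.** Adjustments to protocol cuts the dyads to 15 per country, makes their data mainly qualitative, and bases the new power statement on 300 physicians. The group and country comparison nevertheless remains in the Abstract, in the secondary objectives and in Data analyses, and the Discussion lists comparison of the three perspectives as a strength.

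**The concern.** Ordinary logistic regression with group and country as factors takes the observations as independent. Here 30 of every 80 respondents belong to pairs who share a household or family, a visit and, on one measure, the person being asked about. If answers within a pair agree more often than chance, two things follow.

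- The person-with-dementia versus caregiver difference is a within-pair comparison. Shared variation cancels, so its true standard error is smaller than the model reports, and real differences are easier to miss.
- A country mean adds the two members together. Shared variation accumulates, so the true standard error of a country contrast is larger than reported, and false-positive findings are somewhat more frequent than 5%.

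The first effect is the larger. It falls on the group whose views the Background describes as least known, with only 90 persons with dementia planned in total.

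**Working it through.** **The plan's own counts.** Original target: 6 countries × 3 groups × 50 = 900; a 10% rate gives 90 events. Amended: 6 × 50 = 300 physicians, and 7 variables × 10 events = 70 events. Both reproduce. Neither uses a within-pair correlation, and the amended one contains no dyads.

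**Inputs for the check**
- Amended sample per country: 50 + 15 + 15 = 80, of whom 30 are in dyads (30/80 = 0.375). In total 6 × 80 = 480 respondents, of whom 180 form 90 pairs.
- Within-pair correlation ρ of the binary answers: not given; assumed 0.2 to 0.6.
- Two-sided alpha 0.05: assumed.

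**Formulas** (k = true SE ÷ SE reported by the ordinary model)
- Person with dementia vs caregiver: k = √(1 − ρ)
- Country contrast in the pooled model: k = √(1 + 0.375ρ)
- Actual type I error = 2 × [1 − Φ(1.96/k)]

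| ρ | Patient vs caregiver: k | Type I error | Country: k | Type I error |
|---|---|---|---|---|
| 0.2 | √0.8 = 0.89 | 2.8% | √1.075 = 1.04 | 5.9% |
| 0.4 | √0.6 = 0.77 | 1.1% | √1.15 = 1.07 | 6.8% |
| 0.6 | √0.4 = 0.63 | 0.2% | √1.225 = 1.11 | 7.7% |

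**Simulation.** Ordinary logistic regression with 5 country and 2 group indicators, acceptability 50%, correlated pairs, 50 + 15 + 15 per country, 2000 runs per setting:

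| ρ | Patient vs caregiver: k (type I) | Country: k (type I) | Physician vs patient: k (type I) | Physician vs both dyad groups averaged: k (type I) |
|---|---|---|---|---|
| 0.2 | 0.88 (2.2%) | 1.03 (5.6%) | 1.02 (5.6%) | 1.11 (7.6%) |
| 0.4 | 0.79 (1.0%) | 1.08 (6.4%) | 1.01 (5.0%) | 1.14 (7.9%) |
| 0.6 | 0.65 (0.5%) | 1.10 (6.9%) | 1.02 (4.9%) | 1.19 (9.8%) |

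The simulation agrees with the formulas. Physician versus patient is essentially undistorted, because each pair contributes only one member to it; physician versus caregiver follows by symmetry. Averaging the two dyad groups against physicians errs in the same direction as country.

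**Lost power, illustrated.** Assume acceptability of 50% in one dyad group and 35% in the other, with 90 pairs.
- Variances: 0.50 × 0.50 = 0.25 and 0.35 × 0.65 = 0.2275; sum 0.4775.
- Unpaired SE = √(0.4775/90) = 0.0728. The unpaired test rejects when the difference exceeds 1.96 × 0.0728 = 0.143, which gives power of about 54% to 56% over the range of ρ.
- Paired SE = √[(0.4775 − 2ρ√(0.25 × 0.2275))/90], with √(0.25 × 0.2275) = 0.2385.
- ρ = 0.3: SE = 0.0610; power Φ(0.15/0.0610 − 1.96) = 69%.
- ρ = 0.5: SE = 0.0515; power Φ(0.15/0.0515 − 1.96) = 83%.

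**The case against.** **Independence is inferred, not stated.** The article is condensed, its analysis plan is not shown, and the term logistic regression could cover a GEE or mixed model. This stands as a limit on confidence. But Data analyses goes into detail on outcome coding, adjustment covariates, selection method and forced terms, and the original sample size counts each dyad member as a separate respondent. Followed as written, the method does not fit the design.

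**The amendment moved the dyads to the background.** Also true: a regression confined to the 300 physicians has no pairing problem. But no section confines it, and the three-group comparison is still an objective.

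**The affected group contrast carries no hypothesis, and its error is conservative.** Correct. The Hypotheses section makes no prediction comparing persons with dementia with other groups, and too large a standard error creates no false positives. The cost is sensitivity in a secondary comparison. The primary objective is reported descriptively, and its point estimates do not change.

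**The correlation is assumed, and the shared-referent argument covers only one measure.** Both points stand. On general acceptability for dementia care, the pair do not answer about the same person, so the correlation may be lower. The power example also does not carry over to the advance care planning interventions, which the article reports as acceptable to almost all so far.

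**Stronger readings to avoid.** A reader might infer that all group contrasts are wrong; physicians against either dyad group alone are not. A reader might also apply the formula to dyads only, k = √(1 + ρ), and quote type I error of about 8.6% to 11.0% for ρ of 0.3 to 0.5. The article describes no dyad-only country regression, so that figure does not describe its plan.

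**Conclusion.** The concern holds for any model that pools the three groups. With a positive within-pair correlation of 0.2 to 0.6, the reported standard error for person with dementia versus caregiver is too large: the true one is 0.89 to 0.63 of it, and power is lost. Country contrasts err the other way, but modestly: the true standard error is 1.04 to 1.11 times the reported one. Direction and size both rest on the assumed correlation, on alpha of 0.05 and on the 50:15:15 target being met.

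Severity is moderate. The primary descriptive results are untouched, the country distortion is small, and the larger effect is conservative and falls on a secondary comparison without a hypothesis. It is still worth correcting, because the better method costs nothing.

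**What to change.** 1. In Data analyses, state that every model pooling the three groups accounts for the dyad: GEE logistic regression or cluster-robust variance on dyad identifier with physicians as clusters of one, or a dyad random intercept. The first two keep odds ratios on the population-average scale of the ordinary model. Apply this to the stepwise models too.
2. Test person with dementia versus caregiver as a paired comparison (McNemar or conditional logistic regression), or take it from the clustered model.
3. If the regression is now meant for physicians only, say so and describe the dyad answers without pooled tests; points 1 and 2 then fall away.
4. Keep a non-identifying dyad number in the analysis file. Data management and monitoring keeps the participant code list only until cleaning is complete, so the pairing should not depend on that list.

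The cost is a change of analysis wording and one retained variable. Recruitment, sample size and data collection are unchanged, and the pairing is already known because each pair is recruited together.
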